### Statistical analysis

The primary population for efficacy analysis will be the full analysis set, defined as the patients who are administrated investigational product or placebo at least once. The primary endpoint is OS, defined as the time from date of secondary registration to the date of death from any cause. PFS is counted from the date of secondary registration to the date of death without progression, or of progression as confirmed by the Diagnostic Radiology Committee. OS and PFS will be compared using a stratified log-rank test with a two-sided alpha of 0.05 stratified by institution and time of initial apheresis (before, during, or after primary treatment). The HRs and 80% and 95% confidence intervals (CIs) will be estimated by the Cox proportional hazards model. Survival estimation will be also carried out using the Harrington-Fleming test, with the weight proportional to cumulative death probability. For the analysis of cytoreductive effect, adverse events, and side effects, categorical outcomes will be summarized using frequency and percentage for each arm and will be compared using Fisher’s exact method. The odds ratios and 95% CIs will also be estimated.

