
### Sample size

A clinical study by Todaka et al. showed that median survival time of patients refractory to gemcitabine receiving S-1 monotherapy was 5.8 months [19]. Based on this result, the threshold median survival time was defined as 5.8 months. In contrast, a retrospective study by the organization supplying the investigational product (Tella Pharma Inc.) showed that the median survival time of 20 patients receiving dendritic cell vaccine in combination with S-1 as secondary treatment after receiving Gemzar or Gemzar plus S-1 was 8.1 months. However, in this clinical study, the day of starting dendritic cell vaccine therapy was defined as Day 1. Given that it takes approximately 4 weeks to generate dendritic cell vaccine after the collection of cells from patients, approximately 1 month had passed from the time when the patients became refractory to Gemzar or Gemzar plus S-1 to the time of starting the vaccine therapy. In this clinical study, the dendritic cell vaccine is generated during the primary treatment, and the dendritic cell vaccine therapy in combination with S-1 is started immediately after transition to the secondary treatment (this trial). We therefore believe that it is justified to add 1 month (the period required to generate the dendritic cell vaccine) to the median OS reported by Tella Pharma Inc. Accordingly, the expected median OS is set as 9.0 months. If the median OS is 5.8 months for the control group (placebo in combination with S-1) and 9.0 months for the investigational product group (TLP0-001 in combination with S-1), the expected hazard ratio (HR) for the investigational product group relative to the control group is calculated to be 0.644. A log-rank test is used to test the null hypothesis (the HR for the investigational product group relative to the control group is 1) against the one-sided alternative hypothesis (the HR is below 1). Given the assumption of a power of 80% or higher and a two-sided significance level of 0.05, the required minimum sample size was 87 individuals per group. Accordingly, the sample size was set as 90 individuals or more per group (i.e., a total of 185 individuals) with an assumption that a few patients would become ineligible for the trial.

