In a preliminary clinical trial conducted with administration of a dendritic cell vaccine loaded with WT1 peptides, 1 × 10^7^ living dendritic cells were administered intradermally every other week [17]. In this study, five of six patients (83.3%) confirmed the increased induction of WT1-specific CTLs after administration of dendritic cells. TLP0-001 is also considered to cause antitumor activity by inducing WT1-specific CTLs, and as a result of this preliminary clinical trial, the dosage and administration interval of TLP0-001 were determined. This is a placebo-controlled, double-blind, randomized trial to evaluate the superiority of the investigational product (TLP0-001 in combination with S-1) to the control product (placebo in combination with S-1) as the secondary treatment for advanced/recurrent pancreatic cancer, using OS as the endpoint. We are conducting this study in anticipation of the approval, including insurance coverage, of TLP0-001 as a secondary treatment for pancreatic cancer in Japan. This is the first-in-human clinical trial of TLP0-001. Therefore, the trial will be performed with full consideration of safety. To fully assure the safety of the subjects, an interim analysis will be performed when the first six patients of the investigational product group (TLP0-001 in combination with S-1) have completed the first course of treatment, and the safety for the continuation of the trial will be evaluated by the independent Data and Safety Monitoring Committee. The trial is only to be conducted at the Second Department of Surgery at Wakayama Medical University until the safety of the first course has been confirmed by the interim analysis. The procedure requires at least overnight hospitalization from Day 1 for observation.

We plan to conduct a multicenter trial at 18 institutions in Japan after the safety has been confirmed by interim analysis.

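### The sample size is powered for an unstratified log-rank test, but the primary OS test is stratified by institution and apheresis time (up to 54 strata), which lowers power to roughly 55–75%

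*Protocol article*

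**What the plan says.** In the protocol article, the Sample size section sets medians of 5.8 and 9.0 months, from which "the expected hazard ratio (HR) for the investigational product group relative to the control group is calculated to be 0.644". It continues: "A log-rank test is used to test the null hypothesis". No strata are mentioned. "Given the assumption of a power of 80% or higher and a two-sided significance level of 0.05", it reports that "the required minimum sample size was 87 individuals per group", and then "the sample size was set as 90 individuals or more per group (i.e., a total of 185 individuals".

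The Statistical analysis section names a different test for OS and PFS: a "stratified log-rank test with a two-sided alpha of 0.05 stratified by institution and time of initial apheresis (before, during, or after primary treatment".

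The number of institutions is in the Discussion: "We plan to conduct a multicenter trial at 18 institutions in Japan". The Study design section allocates patients 1:1 by Pocock-Simon minimization on the same two factors.

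**The concern.** A stratified log-rank test compares the arms only within strata. A stratum that holds one arm contributes nothing, and in a very small stratum the risk set soon has only one arm left, so later deaths contribute nothing either. With 18 institutions and three apheresis levels there can be 18 × 3 = 54 strata. At that maximum, 185 / 54 = 3.4 patients fall in each. Minimization on the margins does not balance the arms inside these cells.

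The article therefore powers one test and specifies another. OS is the sole primary endpoint, and the Background calls the trial confirmatory and conducted in anticipation of approval. If the assumed hazard ratio is true, the chance of missing it could be well above the 20% that the plan accepts.

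**Working it through.** **Inputs from the article.** Medians 5.8 and 9.0 months; two-sided 0.05; 80% power; 185 patients; 18 institutions; three apheresis levels; recruitment March 2017 to March 2020 (about 36 months; Trial status); outcome survey to 548 days after the last secondary registration (about 18 months; Fig. 1 legend).

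**Assumptions (not in the article).** Exponential survival, uniform accrual, minimization with a biased coin of 0.8, and the distribution of patients over sites and apheresis levels, which is varied below.

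**Step 1: reproduce 87 per group.**
- HR = 5.8 / 9.0 = 0.644; ln HR = −0.4394.
- Schoenfeld: deaths = 4 × (1.960 + 0.842)² / 0.4394² = 162.6, so 163.
- Probability of death by study end, averaged over arms: 0.944.
- 163 / 0.944 / 2 = 86.3, so 87 per group, as stated.
- Freedman's formula gives 168 deaths and 89 per group. A one-sided 0.05 gives only 69–71 per group and does not reproduce the figure.

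**Step 2: unstratified power at 185 patients.** Deaths = 185 × 0.944 = 174.7. Power = Φ(0.4394 × √174.7 / 2 − 1.960) = Φ(0.944) = 82.7%.

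**Step 3: simulate the test as written.** 2,000 trials per row; the Monte Carlo standard error is about 1 point (√(0.57 × 0.43 / 2000) = 0.011). Cells are power in %. The apheresis mix is before/during/after.

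| Site sizes | Apheresis mix | Unstratified | Apheresis only | Institution only | Crossed | Occupied strata |
|---|---|---|---|---|---|---|
| Equal | thirds | 81.5 | 80.3 | 73.2 | 56.8 | 52 |
| Equal | 20/60/20 | 81.4 | 79.8 | 73.0 | 58.4 | 49 |
| Equal | 10/80/10 | 83.5 | 81.8 | 74.9 | 66.4 | 41 |
| Lead site 30%, others equal | thirds | 80.9 | 79.2 | 72.6 | 59.6 | 50 |
| Lead site 30%, others declining | 20/60/20 | 82.9 | 82.0 | 74.8 | 64.5 | 41 |
| Zipf | thirds | 82.8 | 81.8 | 75.4 | 62.4 | 45 |
| Lead site 50%, others declining | 10/80/10 | 81.4 | 80.8 | 75.0 | 70.2 | 31 |

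At 180 patients (90 per group), equal sites and thirds, the crossed test has 54.2%.

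**Step 4: favour the plan.** With the after-treatment level at 0–2% (600 runs, standard error about 2 points), the crossed test has:
- equal sites: 63–69%;
- lead site 30%, others equal: 65–69%;
- lead site 30%, others declining: 70–72%;
- lead site 50%, others declining: 71–76%.

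A further set of 600-run scenarios over such mixes gave 57–75% crossed, 72–79% by institution alone, 78–84% by apheresis time alone and 79–85% unstratified, with about 23–52 strata occupied.

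**Step 5: analytic check.** Power = Φ(0.4394 × √V − 1.960), where V is the log-rank variance.
- Equal sites and thirds: 4V falls from 162.9 unstratified to 92.2 crossed. V = 23.05 gives Φ(0.15) = 56%, against 56.8% simulated.
- Lead site 50%, mix 10/80/10: 4V = 126.5. V = 31.6 gives Φ(0.51) = 70%, against 70.2% simulated.

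**Step 6: type I error.** Under no effect, the crossed test rejected in 5.1% of 2,000 trials (equal sites, thirds). A separate run of 1,200 gave 5.8% with a standard error of 0.6 points. Both are compatible with 5%.

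**Step 7: does prognostic strength repay the strata?** With site effects of SD 0.3 on the log hazard, power was 58–67% crossed, 78–80% unstratified and 78–79% by apheresis time only. With steps of 0.3 across apheresis levels as well (equal sites, thirds), it was 55% crossed, 74% unstratified and 75% by apheresis time only. The loss is not recovered.

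**The case against.** The strongest objection concerns the size of the loss. A reader might infer that the trial will have 54 nearly empty strata, or that its power is a fixed figure below 65%. The article supports neither.

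- Fifty-four is a ceiling. The Sample size section says the vaccine is made during primary treatment, and the Exclusion criteria require enough doses from apheresis done before secondary consent. First apheresis after primary treatment may therefore be rare.
- A dominant lead site is plausible. The trial stays at one centre until the safety interim analysis. In December 2018, 21 of the 36 recruitment months had passed, and the Trial status section still wrote of recruitment elsewhere as yet to come.

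Both features raise power, and this objection stands: only a wide range can be defended. It does not rescue the stated power, since no scenario brought the crossed test to 80%.

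The article also does not say that the factors are crossed. Crossing is the usual reading, and institution alone still falls short at about 72–79%.

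A rule for pooling sparse strata may sit in an analysis plan that is not shown, and its absence from an article is no fault. But the article itself names the test, both factors and all three levels. A pooling rule would change that test.

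Stratifying by the minimization factors is also a coherent principle, and the resulting test is valid. What is at issue is its power.

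**Conclusion.** The point holds as a mismatch between the test that was powered and the test that is specified. The 87 per group and the power of "a power of 80% or higher" belong to an unstratified log-rank test, which has about 82–83% power at 185 patients. With institution and apheresis time crossed, power at HR 0.644 is roughly 55–75%, so the chance of missing the assumed effect is about 25–45% instead of at most 20%. The range assumes site sizes from even to half of all patients at the lead site, an after-treatment level of 0–33%, and a biased coin of 0.8. That the power falls short is firm; by how much is not, because the article gives none of these quantities.

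Two further inferences should be resisted. The test is not anti-conservative: type I error stays near 5%. And the article does not say whether the Cox model is stratified, so matching its strata to the test is a detail for the analysis plan and not part of this error.

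**What to change.** Before unblinding, amend the sentence on the OS and PFS comparison so that the log-rank tests are stratified by time of initial apheresis only. That test had about 78–84% power across the site and apheresis mixes above. It is not a guarantee of 80%: if both factors are prognostic as in Step 7, it has about 75%. Keep institution as a minimization factor and report the institution-stratified test as a sensitivity analysis.

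If the sponsor prefers to keep institution in the primary test, the power should be restated for that test, with the assumed site and apheresis distributions given.

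The change is one sentence and needs no new patients or data. Its downside is that the primary test no longer conditions on every minimization factor; the sensitivity analysis shows whether this matters.

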## Methods

### Aim

The primary objective of this clinical trial is to evaluate the safety and efficacy (as measured by overall survival [OS]) of TLP0–001 in patients with pancreatic cancer refractory or intolerant to standard therapy through a comparison of the control group (placebo in combination with S-1 [tegafur/gimeracil/oteracil]) and the investigational product group (TLP0-001 in combination with S-1).

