### Dosage and administration

The course of treatment with the investigational product in combination with S-1 will be repeated every 6 weeks as one course until the patient meets the discontinuation criteria.

For every course of treatment, S-1 will be administered for 4 weeks and then withdrawn for 2 weeks (i.e., administered every day from Day 1 to Day 28 and then withdrawn from Day 29 to Day 42). The investigational product will be administered every other week (three times, on Day 1, Day 15, and Day 29 of each course).

The investigational product will be manufactured by the organization supplying the investigational product (Tella Pharma Inc., Shinjuku, Tokyo) in accordance with Good Manufacturing Practice. The frozen investigational product will be thawed rapidly in a water bath for approximately 70 s at 37 °C at the time of administration. After the product is thawed, the contents will be directly aspirated with a syringe and administered within 1 h of thawing. The dose of the investigational product will be administered in a volume of 1000 μL. The product will be inoculated intradermally into the axilla and groin in fractional doses of 100 μL by using a syringe.

The initial dose of S-1 will be determined in accordance with the criteria presented in Table 1. S-1 will be administered in two equally divided doses (after breakfast and supper).

**Table 1 Tab1:** Initial dose of S-1

Creatinine clearance^a^	Body surface area	Dose of S-1 (indicated as tegafur dose)
60 mL/min or more	Less than 1.25 m^2^	80 mg/day
	1.25 m^2^ or more, less than 1.5 m^2^	100 mg/day
	1.5 m^2^ or more	120 mg/day
Less than 60 mL/min	Less than 1.25 m^2^	50 mg/day
	1.25 m^2^ or more, less than 1.5 m^2^	80 mg/day
	1.5 m^2^ or more	100 mg/day

^a^Creatinine clearance will be estimated from the Cockcroft-Gault formula, although actual measurement values will be used if available

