### Treatment discontinuation criteriad

The study treatment will be discontinued when a patient meets any of the following criteria during the period of administration of the investigational product:A patient cannot start the first course of study treatment within 15 days after the secondary registration.Aggravation of the primary disease (including clinical aggravation of the primary disease without evident tumor growth by imaging studies) is observed. However, study treatment may be continued if a principal investigator judges that study treatment would be beneficial even in patients judged as having progressive disease according to the Response Evaluation Criteria in Solid Tumors (RECIST) v1.1 Japanese version by the Japan Clinical Oncology Group (JCOG).Diffuse alveolar damage pattern is seen on chest imaging. The presence of a diffuse alveolar damage pattern is confirmed through consultation with respiratory specialists or radiologists in the hospital or specialists in the assessment of pneumonitis.A patient with a lung lesion has pleural effusion which a principal investigator (or co-investigator) judges as difficult to control.When an increase in pleural effusion is seen in patients with carcinomatous pleurisy.When an adverse event that requires discontinuation of the investigational product or S-1 occurs.When a patient cannot start the next course of treatment within 14 days after the scheduled date in the second course or later phases (the scheduled date is 42 days after Day 1 of the previous course. Starting the course 2 weeks after the scheduled date on the same day of the week is allowed)When an adverse event that meets the dose reduction criteria of S-1 occurs after the maximum reduction, and the attending doctor judges that discontinuation of the treatment is neededWhen the attending doctor judges that discontinuation of the treatment is needed because of adverse events other than aboveWhen administration of the investigational product is skipped twice in a rowWhen pregnancy is confirmedWhen a patient requests to withdraw from the trialWhen a patient withdraws his or her consentWhen a patient has difficulty in continuing treatment because of moving, changing hospital, or otherwise being unable to attendWhen a patient is found to be ineligible after registration

The study treatment will also be discontinued when a principal investigator judges that it is necessary for any other reason.

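### Adverse events are compared by crude percentages and Fisher's test although treatment is open-ended; if time on treatment differs by arm, events that accrue over time will differ even at equal monthly rates

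*Protocol article*

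**What the plan says.** All references are to the protocol article.

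- **Statistical analysis.** For cytoreductive effect, adverse events and side effects alike, "categorical outcomes will be summarized using frequency and percentage for each arm"; the arms are then compared by Fisher's exact method. The section adds: "The odds ratios and 95% CIs will also be estimated". It names no person-time, time-to-event or fixed-window method for adverse events.
- **Dosage and administration.** Treatment is "repeated every 6 weeks as one course until the patient meets the discontinuation criteria". No maximum number of courses is stated. S-1 is given in both arms within the same courses.
- **Treatment discontinuation criteria.** One reason to stop is "Aggravation of the primary disease (including clinical aggravation of the primary disease without evident tumor growth by imaging studies) is observed". Even so, "study treatment may be continued if a principal investigator judges that study treatment would be beneficial" in patients who have progressed by RECIST.
- **Aim.** "The primary objective of this clinical trial is to evaluate the safety and efficacy", by comparing the two groups.
- **Endpoints.** The primary endpoint is overall survival (OS) alone; safety endpoints are listed separately. The one safety stopping rule is the interim rule on dose-limiting toxicity in the first course, in six patients of the investigational product group.

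**The concern.** An ever/never percentage treats a patient observed on treatment for one course and a patient observed for five as equally at risk. That does little harm when exposure is alike in both arms. Here exposure depends on the course of the disease, because aggravation ends treatment. A vaccine that delays stopping lengthens exposure to the vaccine and also to S-1, so that arm collects more patients with at least one event, including events due to S-1. Fisher's test and the odds ratio would show this as an excess on the vaccine. If the vaccine shortened treatment, the same method would hide a real excess.

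The comparison matters because safety is named in the primary objective and this is a first-in-human trial. The interim look uses a common early window, but it covers six patients of one arm and makes no between-arm comparison. The crude Fisher comparison is therefore the only controlled safety comparison that the article describes.

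**Working it through.** **The plan's own figure.** The Sample size section states that "the expected hazard ratio (HR) for the investigational product group relative to the control group is calculated to be 0.644". Check: 5.8/9.0 = 0.644, and the inverse is 9.0/5.8 = 1.55. Both medians are OS medians. The article gives no figure for treatment duration, progression-free survival (PFS) or adverse event rates, so every exposure ratio below is an assumption.

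**Model.** Event rate r per month is identical in both arms. Time on treatment is exponential with median m, so treatment stops at rate ln2/m. Then

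P(at least one event) = r / (r + ln2/m), and the odds are r × m / ln2.

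The crude odds ratio therefore equals the exposure ratio, while the true rate ratio is 1.00.

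**Example.** Take r = 0.10, control median 4 months and exposure ratio 1.55 (vaccine median 4 × 9.0/5.8 = 6.2 months).
- Control: 0.10/(0.10 + 0.173) = 37%.
- Vaccine: 0.10/(0.10 + 0.112) = 47%.
- Odds ratio 1.55, with no difference in toxicity per month.

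**How often Fisher's test gives p<0.05.** Exact enumeration, two-sided, 185 patients split 93 (vaccine) and 92 (control), r = 0.05-0.20, control median exposure 2.5-5.8 months:

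| Exposure ratio | Trials with p<0.05 |
|---|---|
| 1.0 | about 4% |
| 1.1 | about 4-5% |
| 1.2 | 6-8% |
| 1.35 | 9-15% |
| 1.55 | 17-28% |

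With the odd patient in the control arm instead, only the lower ends move, to about 7%, 11% and 20% in the last three rows.

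**A second calculation: false excess on the vaccine only.** With 90 per arm and an exposure ratio of 1.55, control percentages of 10/20/30/50/70% become 14.7/28.0/39.9/60.8/78.4%. A significant excess is declared with probability 0.115/0.189/0.240/0.251/0.200, against 0.015-0.017 at equal exposure.

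**Events confined to the first course (42 days).** With a control median of 2.5 months and ratio 1.55, control percentages of 10/30/50% become 10.7/31.8/52.8%. The probability of a significant excess is 0.022/0.032/0.038. Counting both directions, p<0.05 occurs in about 3-5% of trials, which is essentially no inflation.

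**Does an early window cure it?** Within a window of w months and with h = r + ln2/m, P = (r/h)(1 − e^(−hw)). Take r = 0.20, medians 2.5 and 3.9 months, and 30.4 days per month.
- Day 1-84 (w = 2.76): 30.7% vs 34.2%, odds ratio 1.18. Only 2^(−2.76/2.5) = 47% of control patients are still on treatment at the end of the window.
- Day 1-42 (w = 1.38): 20.2% vs 21.5%, odds ratio 1.08.

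Over the full range of rates and medians, the Day 1-84 odds ratio is 1.06-1.18.

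**The case against.** **This is standard practice, and a statistical analysis plan may add more.** Crude incidence tables are the usual oncology display, and exposure-adjusted rates are often left to the analysis plan. That stands as far as the table goes: the table is not wrong, and nothing is held to be missing. What remains is that the article itself fixes a between-arm test and effect measure that ignore time at risk.

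**The ratio 1.55 is not the trial's assumption about exposure.** This stands in full. A reader might infer that the plan's own alternative makes the safety comparison biased against the vaccine. The documents do not support that: the alternative concerns OS only. PFS is a secondary endpoint with no hypothesised effect, and survival can improve with little change in time on treatment. Several stopping criteria besides progression, such as toxicity, course delay and two skipped doses in a row, may also keep exposure close between arms. Product supply could do the same, since the exclusion criteria ask only that five doses can be made and a course uses three.

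**The constant rate is an assumption, and the collection window is not visible.** Both points stand. For early events the distortion almost vanishes, and the safety schedule (Table 2) is not shown.

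**Little hangs on the p-value.** A reader might infer from the Aim that this test decides half of the primary objective. It does not: OS is the sole primary endpoint, no decision rule is attached to the Fisher result, and the interim toxicity rule is unaffected.

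**Conclusion.** The point holds as a minor one, in conditional form. The stated comparison confuses event rate with time on treatment whenever exposure differs between arms and events accrue throughout treatment. At equal monthly rates, the chance of p<0.05 for one adverse event type is close to nominal for exposure ratios up to about 1.1. It rises modestly at 1.2 and is several times nominal only towards 1.55, which is an upper illustration. The direction is not fixed: longer vaccine exposure exaggerates toxicity, and shorter exposure masks it. These results rest on exponential exposure, a constant event rate and counting events over time on treatment, none of which the documents state. The sample size and the primary OS test are not affected.

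**What to change.** 1. Keep the crude table of frequencies and percentages as description.
2. Base the between-arm safety comparison on exposure-adjusted incidence: events per patient-month with a rate ratio and 95% confidence interval. Under the model above its expected value is about 1.00.
3. Add time to first grade 3 or higher event. State in advance how the end of the adverse event risk period and death are handled. Censoring at these points compares event rates. Treating them as competing events gives absolute risk, which still carries the exposure difference, so the two should not be read as the same result.
4. If an early common window is wanted, use the first course (Day 1-42), or analyse the window by time at risk. Crude percentages over Day 1-84 are not fully comparable when many patients stop earlier.

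The cost is a few extra tables from treatment and event dates, and a constant-rate assumption for the rate ratio. The choice should be recorded before unblinding, because an adjustment introduced after an imbalance has been seen would look post hoc.
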